#### Participation incentives

All participants will be provided with single-ride public transportation cards to attend classes and study visits as needed. All study participants will receive a $20 gift card after completing the baseline assessment, and a $30 gift card after completing each of the 2-, 4-, and 6-month assessments for a total of $110 in gift cards for full participation. All M-Body participants will receive an instructional manual and audio CD, yoga mat, tote bag, and pen for use inside and outside of group sessions. Light meals will be provided at each of the in-person sessions.

### Randomization

Following consent but prior to randomization, participants will complete a clinical interview and baseline surveys, and stress biomarker data will be collected. We will then implement a block randomization procedure, with each participant in a cohort randomly assigned to 1 of the 2 arms (overall allocation ratio, 1:1). Block randomization with randomly varying block sizes was chosen to prevent prediction of assignments and thereby protect from selection bias. Randomization will be stratified by gender, initial severity of depression (Inventory of Depressive Symptomatology- Clinician Administered (IDS-C) ≥38), and receipt of treatment for depressive symptoms (antidepressants and/or psychotherapy versus none) [62]. To avoid all possibility of interference from the investigators, randomization will be fully automated, with the randomization sequence prespecified in R [63] and implemented through Research Electronic Data Capture (REDCap) [64, 65]. After randomization, research staff will provide participants with a sealed envelope containing their condition assignment. Neither the participants, study coordinators, statistical analysis team, nor the treatment providers will be blinded to treatment assignments. Independent evaluators and study co-investigators will remain blinded. To maintain the overall quality and legitimacy of the clinical trial, unblinding should occur only in exceptional circumstances when knowledge of the actual treatment is absolutely essential for further management of the participant. The Principal Investigator will discuss with the co-investigators and DSMB if she believes that unblinding is necessary.

### Retention and adherence strategies

To enhance recruitment and recognize the contributions of participants in the UC condition, these individuals will be invited to participate in the M-Body group at the end of 6 months after all data have been collected. To improve engagement in the intervention, the research staff will phone, email, or text subjects whenever they miss a session to encourage participation. Reminders will be sent to all participants to remind them of upcoming data collection and the incentives they will receive. The study team will make every effort to be flexible and accommodate participant schedules.

### Measures

For a brief overview of all measures and assessment times, see Table 3.

**Table 3 Tab3:** Instruments used to collect data during the M-Body study

			Scoring			Visit administered^a^				
Instrument	Construct(s) measured	Reliability/validity^b^	No. items	Score range	Interpretation	T0	T1	T2	T3	T4
*Primary outcome*										
Structured interview guide for the inventory of depressive symptomology (Clinician-rated) Rush et al., 1986 [62]	Depressive symptoms	High/moderate Rush et al., 1986 [62]	30	0–84	0–13 = None 14–25 = Mild 26–38 = Moderate 39–48 = Severe 49–84 = Very Severe		x	x	x	x
*Secondary outcomes*										
Generalized anxiety disorder - 7-item scale Spitzer et al., 2006 [66]	Generalized anxiety	High Spitzer et al., 2006 [66]	7	0–28	5 = Mild 10 = Moderate 15 = Severe ≥10 indicates probable GAD diagnosis		x	x	x	x
Anger self-report questionnaire Reynolds et al., 1994 [67]	Anger	High/moderate Reynolds et al., 1994 [67]	30	30–180	Higher scores indicate increased trait anger		x	x	x	x
Posttraumatic stress disorder (PTSD) for DSM-5 (PCL-5) Weathers, et al., 2013 [68]	Trauma; PTSD symptom severity	High Blevins et al., 2015 [69]	20	0–80	≥31 indicates probable PTSD diagnosis		x			x
*Other psychological assessments*										
Patient Health Questionnaire-9-item Kroenke et al., 2001 [70]	Depression	High Kroenke et al., 2001 [70]	9	0–27	1–4 = Minimal 5–9 = Mild 10–14 = Moderate 15–19 = Moderately severe 20–27 = Severe	x				
Mini International Neuropsychiatric Interview Sheehan et al., 1998 [71]	Major depressive episode(s), Dysthymia, Generalized Anxiety Disorder	High Sheehan et al., 1998 [71]	46	N/A	N/A		x			
Longitudinal Interval Follow-up Evaluation – II (Modified) Keller et al., 1987 [72]	Major Depressive Episode(s), Dysthymia, Generalized Anxiety Disorder	High Keller et al., 1987 [72]	22	0–48	A coding of 5 and above indicate meeting DSM-IV criteria.			x	x	x
HIV cost and services utilization study baseline questionnaire, module 6: utilization of care—modified Shapiro et al., 1999 [73]	Mental health providers, social support, usual source of medical care, utilization of care and services used	N/A	44	N/A	N/A		x	x	x	x
Social problems questionnaire (Modified) Corney and Clare 1985 [74]	Social problems, difficulties and dissatisfactions	N/A	28	0–112	Higher scores indicate greater social difficulties		x			
Perceived stress scale Cohen et al., 1983 [75]	Perceived helpfulness and perceived self-efficacy	High/moderate Cohen et al., 1983 [75]	10	0–40	Higher scores indicate greater perceived stress		x	x	x	x
Life events checklist for DSM-5 (LEC-5) Weathers, et al., 2013 [76]	Exposure to events known	High Gray et al., 2004 [77]	17	N/A	N/A		x			x
Criterion A extended assessment (from PCL-5 with LEC-5 and Criterion A) Weathers, et al., 2013 [68]	PTSD Criterion A stressor information	N/A	9	N/A	N/A		x			x
Five facet mindfulness questionnaire Baer et al., 2006 [78]	Mindfulness: Observing, describing, acting with awareness, non-judging of inner experience, non-reactivity to inner experience	High Baer et al., 2006 [78]	39	39–195	Higher scores indicate greater trait-like mindfulness tendencies		x	x	x	x
Reflection and rumination questionnaire Trapnell and Campbell, 1999 [79]	Rumination and reflection	High Trapnell and Campbell, 1999 [79]	24	12–60	Higher scores indicate increased rumination		x	x	x	x
Difficulties in emotion regulation scale—short form Kaufman et al., 2016 [80]	Emotion regulation: non-acceptance of emotional response. Difficulties engaging in goal-directed behavior, impulsive control difficulties, lack of emotional awareness, limited access to emotion regulation strategies, lack of emotional clarity	High Kaufman et al., 2016 [80]	18	18–90	Higher scores indicate greater difficulties with emotion regulation		x	x	x	x
Cognitive emotion regulation questionnaire – short form Garnefski et al., 2001 [81]	Cognitive emotion: self-blame, other-blame, ruination, catastrophizing, putting into perspective, positive refocusing, positive reappraisal, acceptance and planning	High/moderate Garnefski et al., 2001 [81]	18	18–90	Higher scores indicate greater use of cognitive strategy		x	x	x	x
Self-compassion scale—short form Raes et al., 2011 [82]	Self-compassion: Self-kindness, self-judgment, common humanity, isolation, mindfulness, over-identified	Moderate Raes et al., 2011 [82]	12	12–60	Higher scores reflect greater self-compassion		x	x	x	x
Spirituality scale Delaney, 2003 [83]	Spirituality; spiritual beliefs, intuitions, lifestyle choices, practices, and rituals	High Delaney, 2003 [83]	23	23–138	Higher scores reflect greater reported experience of spirituality		x			
*Implementation measures*										
Implementation Questionnaire	Attitudes toward implementation of intervention	N/A	8	N/A			x			
Implementation Leadership Scale (Modified) Aarons et al., 2014 [84]	Implementation leadership	High Aarons et al., 2014 [84]	7	0–48			x	x	x	x
Evidence-Based Practice Attitude Scale Aarons, 2004 [85]	Attitudes toward adoption of evidence-based practices	High Aarons, 2004 [85]	15	0–60			x			
Clinical Effectiveness and Evidence-Based Practice Questionnaire (Modified) Upton and Lewis, 1998 [86]	Professional’s attitudes toward concepts and application of evidence-based practice and clinical effectiveness	High Upton and Lewis, 1998 [86]	3	0–24			x	x	x	x

*Abbreviations: No.* number of, *HIV* human immunodeficiency virus, *DSM-5* Diagnostic and Statistical Manual of Mental Disorders, 5^th^ Edition, *DSM-IV* Diagnostic and Statistical Manual of Mental Disorders, 4^th^ Edition

^a^The visit abbreviations “T0,” “T1,” “T2,” “T3,” and “T4” correspond to screening, baseline, and 2-, 4-, and 6-month follow-ups

^b^Low (*α* < 0.60, *κ* < 0.41, ICC < 0.50, *r* < 0.35), moderate (0.60 < *α* < 0.70, 0.41 < *κ* < 0.60, 0.50 < ICC < 0.75, 0.36 < *r* < 0.67), high (*α* > 0.70, *κ* > 0.60, 0.75 > ICC > 0.90, *r* > 0.90) (100, 101, 102, 103)

#### Primary outcome

Depressive symptoms, measured 6 months after baseline, will be the primary outcome of this study, assessed using the Inventory of Depressive Symptomatology- Clinician Administered (IDS-C) [87]. The IDS-C is a 30-item scale that was administered by an independent evaluator who is blind to study condition at baseline and 2, 4, and 6 months. The IDS-C has high internal consistency with a Cronbach’s alpha of .92 [87]. The Longitudinal Interval Follow-up Evaluation – II (LIFE) will be used to assess symptoms at follow-up periods [72].

#### Secondary outcomes

Major depressive disorder and persistent depressive disorder will also be assessed as a secondary outcome using The Mini International Neuropsychiatric Interview (MINI 6.0) at *baseline* [71]. The MINI is a short clinician-administered diagnostic interview that assesses current and lifetime psychiatric disorders based on the American Psychiatric Association’s Diagnostic and Statistical Manual of Mental Disorders – 4^th^ edition (DSM-IV) and International Classification of Diseases (ICD-10) [71]. Study team members administering the MINI were trained by an expert clinician and rated mock interviews until they reached acceptable reliability with the expert clinician.

Longitudinal measures of depressive symptoms, generalized anxiety, anger, and trauma symptoms will also be secondary outcomes (Table 3). Generalized anxiety will be measured using the Generalized Anxiety Disorder-7 Scale (GAD-7) [66]. The GAD-7 is a 7-item self-report measure of generalized anxiety symptoms. Scores of 10 or greater are predictive of a likely GAD diagnosis. Anger will be measured using the Anger Self-Report Questionnaire, which is a single-factor, 30-item self-report measure of anger [67]. Both anxiety and anger will be assessed by self-report at baseline and 2, 4, and 6 months. Post-traumatic stress will be measured using the PTSD Checklist for DSM-5 (PCL-5) [68]. The PCL-5 is a 20-item self-report measure of PTSD symptom severity, administered at baseline and 6 months.

#### Process outcomes

M-Body group audio/video recordings will be used in intervention fidelity assessments. Coders will review the audio/video recordings of the M-Body sessions and assess fidelity, adherence, and competence using the Mindfulness-based Interventions – Teaching and Assessment Criteria scale [88]. Fidelity assessments will be completed for each instructor, each session, for every group for the duration of the study. These data will be used to monitor fidelity to intervention delivery and improve staff training.

Over the course of the M-Body study, all stakeholders will complete measures to assess implementation readiness, feasibility, and fidelity. Stakeholders will include the FQHC Medical Director, Director of Behavioral Health, Director of Quality Assurance Improvement, Instructors, and any other FQHC staff who will be directly involved in the research study. A complete list of implementation measures can be found in Table 3.

#### Covariates, moderators, and mediators

A secondary aim of this study is to investigate M-Body effects on specified biological, psychological, and socio-environmental mechanisms. To this end, we will collect data in three realms: social and environmental factors, psychological outcomes, and stress-related biomarkers.

We will consider age, socioeconomic characteristics, and social and environmental factors as potential moderators of the intervention effects. Socioeconomic characteristics will include education (high school diploma or less versus some college or more), employment (unemployed, part-time, full-time), and income (below versus above the federal poverty line). Social and environmental factors will be assessed at study baseline using (1) the Social Problems Questionnaire (SPQ) as a proxy for environmental stress; (2) spirituality; (3) social support; and (4) a summary of traumatic life events via the PTSD Checklist for DSM-5 with Life Events Checklist for DSM-5 (LEC-5) and Extended Criterion A as a proxy for long-term stress.

Potential mediators will include the following: (1) mindfulness measured via Five Facet Mindfulness Questionnaire (FFMQ); (2) stress, measured via Perceived Stress Scale; (3) Cognitive Regulation measured via Cognitive and Emotion Regulation Questionnaire (CERQ-SF); (4) Emotion Regulation measured via Difficulties in Emotion Regulation Scale (DERS-SF); (5) Reflection and Rumination measured via Reflection and Rumination Questionnaire; (6) Self-Compassion via Self Compassion Scale; and (7) stress-related inflammatory biomarkers, including c-reactive protein (CRP), interleukin-6 (IL-6), tumor necrosis factor-α (TNF-α), and IL-10.

Stress-related inflammatory biomarkers will be analyzed using dried blood spot (DBS) samples. Trained study personnel will collect one to five drops of free-flowing capillary blood on standardized filter paper of the same grade used for neonatal screening using a disposable and sterile micro-lancet. Samples will be covered and left to dry overnight and then frozen at −30 °C until analyzed. Samples will be analyzed for CRP using a high-sensitivity enzyme-linked immunosorbent assay (ELISA) previously validated for DBS. IL-6, TNF-α, and IL-10 will be quantified using a highly sensitive multiplex electrochemiluminescent immunoassay that allows for the simultaneous quantification of each cytokine in DBS. The protocol has excellent lower limits of detection (0.2 to 0.7 pg/mL), precision (intra-assay CVs<7.5%), and reliability (inter-assay CV<9%) and high correlations between matched plasma and DBS samples across the entire assay range. We will be applying standard laboratory quality control procedures, including running samples in duplicate, inspecting calibration curves for fit and day-to-day variation, and measuring quality control samples with each assay.

#### Data collection, quality control, and confidentiality

Data handling procedures for data transfer, entry, and maintenance will be performed by trained study personnel under the supervision of Northwestern Information Technology Services. Self-reported data will be collected via online assessment directly into a Northwestern University-hosted REDCap database. We will collect information at every stage of recruitment, randomization, and intervention so that we can report patient flow according to the CONSORT (CONsolidated Standards Of Reporting Trials) guidelines [89].

#### Protection of human participants and assessment of safety

This trial will be monitored for safety by an independent Data and Safety Monitoring Board (DSMB), composed of two professors of psychology and one psychiatrist with expertise in randomized controlled trials, mood disorders, women’s mental health, and mindfulness interventions. Protocol violations, including inadequate or delinquent informed consent, failure to satisfy inclusion criteria, improper unblinding, incorrect or missing baseline assessments, mishandled samples, materially inadequate record keeping, missed primary outcome data collection, intentional deviation from protocol, Good Clinical Practice (GCP), or regulations by study personnel, and repeated protocol non-compliance will be reported to the Northwestern IRB immediately. Serious adverse events (SAEs), including psychiatric hospitalization determined to be study related, major adverse cardiac events (stroke, myocardial infarction), and death, will be reported to the IRB by filing a report on the Northwestern IRB website. The trial will be stopped if the DSMB determines that there is a risk of SAEs in the intervention arm; in this case, the DSMB has power to recommend study continuation, modification, or termination the study.

Spirit reporting guidelines are being followed in the conduct of this trial [90].

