##### Secondary outcome analyses

We will conduct four exploratory secondary outcome analyses, one each for depression, anxiety, anger, and trauma, designed to leverage the longitudinal nature of outcome assessment in this study. The first will consist of a LMM in which IDS-C will be compared across study arms at each follow-up visit (three fixed effects), controlling for gender, baseline IDS-C scores, and baseline receipt of psychotherapy. Here we will include random effects for group participation and individual, as we will need to account for within-person correlation. We will consider a simpler model for parsimony including follow-up visit as a continuous variable, as in a linear growth mixed effects model, and select the model that minimizes the Bayesian Information Criterion. The visit-specific coefficients on study arm will address the question: “for two patients with the same baseline depressive symptoms, gender, and baseline receipt of psychotherapy, if one is given the M-Body intervention and the other enhanced usual care, will the patients have different depressive symptoms after 2, 4, and/or 6 months?” The secondary outcome analyses for GAD and anger will use similar models to those described here for IDS-C, this time additionally including baseline GAD or anger scores as appropriate. The secondary outcome analysis for trauma will consist of a linear mixed model (LMM) in which mean 6-month trauma will be compared across study arms (fixed effect), controlling for gender, baseline IDS-C scores, and baseline receipt of psychotherapy, with a random group effect. If issues with model convergence are encountered, we will consider simpler models, such as a linear model with fixed effects for groups, or a linear model with no group effects specified. No interim analysis is planned or will take place; we do not anticipate study developments to require interim analyses.

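### The safety stopping sentence gives two incompatible outcomes for one trigger, and the listed SAEs admit psychiatric hospitalisation only when it is judged study related

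*Protocol article*

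**What the plan says.** The protocol article, under Protection of human participants and assessment of safety, sets up an independent DSMB and makes two statements that matter here.

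- **Stopping.** "The trial will be stopped if the DSMB determines that there is a risk of SAEs in the intervention arm"; then, after a semicolon, "in this case, the DSMB has power to recommend study continuation, modification, or termination the study".
- **Reporting.** Serious adverse events are described as "including psychiatric hospitalization determined to be study related, major adverse cardiac events (stroke, myocardial infarction), and death", and these "will be reported to the IRB by filing a report on the Northwestern IRB website".

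Under Randomization: "Neither the participants, study coordinators, statistical analysis team, nor the treatment providers will be blinded to treatment assignments". The next sentence adds: "Independent evaluators and study co-investigators will remain blinded". Under Secondary outcome analyses: "No interim analysis is planned or will take place".

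The article gives no expected SAE rate. It does not say who judges relatedness, or whether the DSMB receives events from both arms. A full protocol or DSMB charter may cover these matters, and their absence from a condensed article is not the point made here.

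**The concern.** Three features of the printed text raise the question.

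1. The two halves of the stopping sentence attach different consequences to the same determination, so a DSMB member cannot tell whether that determination binds the trial or only opens a recommendation.
2. The trigger names one arm of a randomised trial, although the events listed can occur in either arm.
3. Of the listed SAEs, only psychiatric hospitalisation must pass a relatedness judgement. In a depression trial it is the listed event closest to the disease under study, and several groups of people around the participant know the allocation.

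What is at stake is participant safety and the readability of the safety data, not the efficacy analysis. With no interim analysis planned, DSMB review is the main independent check on accumulating harm that the article describes.

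**Working it through.** The plan states no threshold, rate or boundary for safety, so there is no figure to reproduce. Steps 1 and 3 compare passages; steps 2 and 4 are illustrations with assumed rates.

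**Step 1. The stopping sentence.** First half: the DSMB finds a risk in the M-Body arm, and the consequence is that the trial stops. Second half: the opening words point back to that same finding, and the consequence is a recommendation with three options, one of which is to continue. A compulsory stop and a recommendation to continue cannot both follow from one finding unless something is added, for example that stopping means a temporary halt. The sentence does not say so.

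**Step 2. A one-arm trigger.** Inputs: 274 participants (Sample size) at 1:1 (Randomization), so 274 / 2 = 137 per arm. The SAE risk p is assumed, from 0.5% to 5%. The chance of at least one SAE in the M-Body arm is 1 − (1 − p)^137:

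| Assumed p | Expected SAEs, 137p | Chance of at least one |
|---|---|---|
| 0.5% | 0.7 | 50% |
| 1% | 1.4 | 75% |
| 2% | 2.7 | 94% |
| 5% | 6.9 | 99.9% |

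These figures hold with no treatment effect at all. Some M-Body events are likely from background risk, so events in that arm alone say little about harm caused by the intervention.

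**Step 3. The relatedness condition.** "psychiatric hospitalization determined to be study related" stands in the same list as death, stroke and myocardial infarction, which carry no condition. Those who know the arm are participants, coordinators, the statistical team and treatment providers. Those kept blind are independent evaluators and co-investigators. The person who decides relatedness is not named, so either group could supply that judgement.

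**Step 4. What a filter could do.** Let the true hospitalisation risk p be equal in both arms, and let a1 and a0 be the shares judged related in M-Body and usual care. Expected counted events are 137·p·a1 and 137·p·a0. The last column is the exact binomial probability that M-Body shows the larger count. All of p, a1 and a0 are assumed.

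| p | True events per arm | a1 / a0 | Counted, M-Body vs usual care | M-Body shows more |
|---|---|---|---|---|
| 5% | 6.9 | 100% / 100% | 6.9 vs 6.9 | 44% |
| 5% | 6.9 | 25% / 25% | 1.7 vs 1.7 | 39% |
| 5% | 6.9 | 50% / 10% | 3.4 vs 0.7 | 88% |
| 2% | 2.7 | 100% / 100% | 2.7 vs 2.7 | 41% |
| 2% | 2.7 | 25% / 25% | 0.7 vs 0.7 | 31% |
| 2% | 2.7 | 50% / 10% | 1.4 vs 0.3 | 66% |

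With equal shares the filter removes events but creates no expected imbalance. With unequal shares it does. The arms are of equal size, so exchanging a1 and a0 exchanges the columns: under-attribution in M-Body would make M-Body look safer by the same amount.

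**The case against.** The strongest reply is that most of the harm lies outside the text. The relatedness condition belongs to the sentence on IRB reports, not to the stopping sentence. The list is introduced as examples, so it is not exhaustive. What the DSMB receives is not described, and unfiltered listings from both arms are not ruled out. By-arm tables usually sit in a charter. All of this stands.

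It defeats one inference a reader might draw, that the DSMB will see a signal tilted against M-Body. That would need relatedness to be judged differently by arm, and the board to see only the filtered events. The article states neither. Nor is the direction fixed: staff could under-attribute M-Body events as easily as over-attribute them. It would also be wrong to suppose that nothing in usual care could be called study related. Both arms undergo interviews, trauma questionnaires and blood sampling, and usual-care participants receive feedback on their depression score.

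Two further readings fail. A reader might infer that a single unrelated death in the M-Body arm ends the trial, but the trigger is a board determination, not an event count. A reader might also infer that the second half leaves no way to stop, but termination is one of its options.

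Finally, the sentence could be read as a halt pending a recommendation. That is a possible meaning, but the reader has to supply it. It shows that the sentence needs rewriting, not that it is consistent.

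**Conclusion.** The concern holds in limited form. The contradiction in the stopping sentence is in the printed text and rests on no assumption. So do the one-arm wording of the trigger and the condition placed on psychiatric hospitalisation alone.

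That the condition could distort the safety counts is a possibility, not a finding. It depends on relatedness being judged with knowledge of the arm and on only filtered events being reviewed. Under assumed risks of 2% to 5%, the effect runs from no expected imbalance with equal attribution to 3.4 against 0.7 events with unequal attribution, and it could run either way. The documents do not fix its size or direction. No efficacy result or stated figure is affected.

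**What to change.** 1. Reconcile the two halves of the stopping sentence so that one determination has one stated consequence. This review does not say which half is right and proposes no trigger.
2. Record all psychiatric hospitalisations, deaths and cardiac events in both arms, and list them by arm for the DSMB whatever the relatedness judgement, with relatedness as a separate column. The judgement is then kept but no longer decides which events are seen. If the DSMB charter already provides this listing, only the sentence needs changing.

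The cost is one amended sentence, a few more events to record and one more table. No extra visits or staff are needed.
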